# Implementation and real-world effectiveness of a weighted blanket intervention and standard melatonin treatment for children with ADHD and sleep problems: protocol for a pragmatic longitudinal cohort study

**DOI:** 10.1186/s12888-026-08538-4

**Published:** 2026-08-25

**Keywords:** Attention-deficit/hyperactivity disorder, Children, Children’s sleep habits questionnaire (CSHQ), EQ-5D-Y-3L, Health, Implementation, Melatonin, Sleep intervention, Weighted blanket

## Abstract

**Background:**

Sleep problems are common in children with attention-deficit/hyperactivity disorder (ADHD), yet the real-world use, implementation, and long-term outcomes of weighted blankets and standard melatonin treatment remain understudied. This study protocol describes a research project evaluating the real-world effectiveness and implementation of a weighted blanket intervention and standard melatonin treatment for children with ADHD and sleep problems in routine clinical practice. The project focuses on (1) changes over time in sleep, health-related outcomes, and resource utilization within and across treatment arms, and (2) barriers and facilitators to implementation in routine clinical practice.

**Methods:**

The research project uses: (1) a pragmatic longitudinal cohort design to investigate real-world changes over time in sleep, health-related outcomes, and healthcare resource utilization among children receiving either a weighted blanket intervention or standard melatonin treatment, and (2) a process evaluation design to evaluate implementation in routine clinical practice. Approximately 150 child-parent dyads will be included in each treatment arm. Children aged 6–14 years and one of their parents will each complete questionnaires at baseline, before treatment starts, at 1, 3, 6, and 12 months, and then annually for an additional nine years. The questionnaires assess sleep problems using the Children’s Sleep Habits Questionnaire (CSHQ) total score as the primary sleep outcome, treatment adherence and treatment changes, additional sleep-related measures, everyday function, lifestyle habits, worry and anxiety, ADHD-related symptoms, health-related quality of life, pain, resource utilization, and treatment use and implementation. Child-parent dyads and clinical staff members will be interviewed at 6 and 12 months. Appropriate parametric and non-parametric statistical tests will be performed. Interviews will be analyzed using qualitative content analysis. The implementation process will be analyzed using a convergent parallel mixed methods approach.

**Discussion:**

The project has the potential to inform clinical guidelines and decision-making frameworks for personalized care for children with ADHD. By evaluating patterns of treatment use and treatment change, real-world outcomes, and implementation in routine clinical practice, the project may contribute knowledge about the role of weighted blankets as a non-pharmacological treatment option alongside standard melatonin treatment.

**Trial registration:**

http://ClinicalTrials.gov, NCT06808425; registered 29 January 2025.

## Background

Attention-deficit/hyperactivity disorder (ADHD) is a neurodevelopmental condition that involves difficulties with concentration, hyperactivity and impulsivity [1–3]. It affects 6–8% of children [4] and is twice as common among boys as it is among girls (10% vs. 5%) [5]. ADHD negatively affects health-related quality of life [6], school performance [7], and family life [8], and entails significant costs to society [9]. Among children with ADHD, up to 73% experience sleep problems [10], compared to 23% of healthy peers [11], with a higher prevalence among girls than boys (75% vs. 53%) [12]. Sleep problems may be transient, but approximately 10% have persistent problems lasting more than one year [13]. Common sleep problems are bedtime resistance, difficulties falling asleep, nightly awakenings, difficulties with morning awakenings, reduced sleep efficiency, and reduced total sleep time [14, 15], which may lead to daytime sleepiness [16, 17] and negative impact on quality of life, social functioning [16], and ADHD symptoms [15]. Sleep problems in this population also impact negatively on parental mental health [18]. To alleviate ADHD symptoms and facilitate everyday life, children are often treated with stimulants, which can induce or exacerbate sleep problems, such as insomnia [2].

Sleep problems can be treated pharmacologically and/or non-pharmacologically. Prescription of the pharmacological treatment melatonin has increased significantly in Sweden in recent decades [19], and about one third of children with ADHD in Sweden are prescribed sleep medication [20]. Melatonin has demonstrated safety and effectiveness, but side effects such as headache, nausea and fatigue have been reported [21] and long-term effects are insufficiently described. Many parents prefer non-pharmacological treatments to pharmacological treatments [22]. Non-pharmacological treatments commonly include interventions targeted at sleep hygiene, behavioral therapy or sensory aids, such as weighted blankets [23]. Weighted blankets have long been used as a complement to or replacement for pharmacological treatment for children with ADHD and sleep problems [24]. Although widely used in clinical practice, the effects of sleep interventions with weighted blankets have been sparsely studied [25].

In 2020, because of a lack of evidence of their effectiveness, the Medical Technology Product Council in Sweden recommended that weighted blankets for sleep problems should only be prescribed in research studies. This recommendation was then included in the updated treatment guidelines published by the Swedish National Board of Health and Welfare in 2024 [26]. During the same period, our research group conducted a randomized controlled trial in which weighted blankets were compared with lighter control blankets in children with ADHD and sleep problems [27, 28]. Sleep was evaluated both objectively and subjectively by sleep actigraphy, questionnaires, and interviews [27, 29, 30]. Weighted blankets were found to increase total sleep time (mean difference 7.72 min) and sleep efficiency (mean difference 0.82%) and reduce nightly awakenings (mean difference − 2.79 min) and perceived sleep problems compared with the lighter control blankets. They were particularly effective for children 11–14 years of age with the inattentive subtype of ADHD. Results from sleep actigraphy did not support any changes in sleep onset [27]. The children experienced that the weighted blanket required adjustment to individual needs and preferences and adaptation to the environment, improved their ability to regulate worry and anxiety, changed sleep patterns, and promoted functioning in everyday life [29]. Parents experienced improved sleep routines, faster sleep onset, fewer awakenings, and increased well-being in their children, which in turn improved the children’s ability to manage school, leisure activities, and family life [30].

The studies by our research group have established knowledge about the development, feasibility, and evaluation of a weighted blanket sleep intervention for children with ADHD and sleep problems. The final phase, implementation, focuses on how the intervention works in clinical practice [31] to ensure that it is feasible, (cost-)effective, transferable, and scalable. The aim of this study protocol is to describe a research project evaluating the real-world effectiveness and implementation of a weighted blanket intervention and standard melatonin treatment in routine clinical practice for children with ADHD and sleep problems. The project focuses on: (1) effectiveness, including changes in sleep-related outcomes, treatment adherence, health-related outcomes, and resource utilization within and across the initial treatment arms during the first 12 months after inclusion, (2) longer-term patterns of treatment use, adherence, treatment changes, sleep, health-related outcomes, and resource utilization during the annual follow-ups, and (3) barriers and facilitators in implementation in routine clinical practice. We hypothesize that the two initial treatment arms will show different patterns of change in sleep-related outcomes during the first 12 months, but that both groups will improve according to the CSHQ total score. Changes in the standard melatonin treatment arm are expected to primarily concern sleep onset, whereas changes in the weighted blanket intervention arm are expected to concern other aspects of sleep, including total sleep time, nightly awakenings, and perceived sleep quality. We further hypothesize that approximately half of the children starting with a weighted blanket will continue using it at the one-year follow-up. The annual follow-ups will be used to describe longer-term patterns of continued use, discontinuation, switching between treatments, and combined use of weighted blankets and melatonin.

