## Methods

### Study design

The research project uses a pragmatic prospective longitudinal cohort design with two initial treatment arms: a weighted blanket intervention and standard melatonin treatment. Treatment selection will be based on family preference and clinical decision-making in routine clinical practice rather than randomization. Child-parent dyads will be followed from baseline to 12 months, with annual long-term follow-ups for an additional nine years. The rationale for the long-term follow-up is to capture children’s development from childhood through adolescence and into young adulthood. The main evaluation of real-world changes in sleep, treatment adherence, health-related outcomes and resource utilization will focus on the first 12 months after inclusion, whereas the annual long-term follow-ups will be exploratory and used to describe longer-term patterns of treatment use, adherence, treatment changes, sleep, health-related outcomes, and resource utilization. Treatment changes may include continued use, discontinuation, switching between treatments, and combined use of weighted blankets and melatonin. The cohort study is combined with a process evaluation and uses a hybrid type 1 effectiveness–implementation approach [32, 33], in which clinical outcomes are the primary focus and implementation outcomes and contextual determinants are explored in parallel. Quantitative, qualitative, and mixed methods will be used.

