### Participants and recruitment

Children aged 6–14 who are diagnosed with ADHD (according to the Diagnostic and Statistical Manual of Mental Disorders [DSM], Fifth Edition) [34], screen positive for sleep problems, and are patients at the ADHD unit at CAMHS in the south-west of Sweden are eligible for inclusion in the research project. Children with presumed uncomplicated ADHD are triaged to the ADHD unit, whereas children with significant comorbidity or complex psychosocial needs requiring more intensive care are referred to regular CAMHS outpatient care and are not eligible for inclusion [35]. Approximately 350 children with presumed uncomplicated ADHD are seen annually at the ADHD unit, and based on clinical estimates, approximately half of them, about 175 children per year, are expected to screen positive for sleep problems and therefore be potentially eligible for the study. Children, and one of their parents, will be asked to participate in the research project. At inclusion, participants will enter one of two initial treatment arms based on family preference and clinical decision-making: a weighted blanket intervention or standard treatment with melatonin. Recruitment of child-parent dyads is expected to continue until approximately 150 children have been enrolled in each of the weighted blanket intervention and standard melatonin treatment groups.

When families first seek treatment for their child at CAMHS, they have a short telephone interview as part of a structured triage. After triage, the children see a physician for assessment and care planning. If applicable, ADHD medication is also prescribed. At this visit, children and parents receive verbal and written information about the research project and are given a sleep problems screening form to fill out and bring to the follow-up visit.

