The sleep problems screening form is completed by parents and consists of three items from the Swedish version of the Children’s Sleep Habits Questionnaire (CSHQ-SWE) [36, 37]. Each item is scored in terms of 0–1, 2–4, or 5–7 days per week. The items are: “Child falls asleep within 20 minutes after going to bed” (scoring criteria 0–1 or 2–4 days per week), “Child sleeps too little” (scoring criteria 2–4 or 5–7 days per week), and “Child awakes more than once during the night” (scoring criteria 2–4 or 5–7 days per week). Each item contains the follow-up question: “Is this a problem?” (yes / no). If at least one of the items fulfills the scoring criteria and is indicated to be a problem, the child is considered eligible for inclusion.

At the follow-up visit, the sleep problems screening form is assessed by a nurse. If the child fulfills the inclusion criteria of ADHD diagnosis, sleep problems, age 6–14 years, and is a patient at the ADHD unit, and if the child-parent dyad understands written and spoken Swedish, the child-parent dyad is invited to participate in the research project.

Recruitment to the research project will occur continuously and include both newly and previously diagnosed children at the unit, and those who use and do not use ADHD medication. Participants will enter one of two initial treatment arms: (1) weighted blanket or (2) standard treatment with melatonin. During follow-up, participants may continue their initial treatment, discontinue treatment, switch between weighted blanket and melatonin treatment, or use the two treatments in combination, based on family preference and clinical decision-making. Treatment use and treatment changes over time will be documented as part of the pragmatic evaluation.

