### Data analysis

#### Quantitative methods

Data analysis will be performed using IBM SPSS Statistics software v.28 or later (IBM Corp., Armonk, NY, USA). Continuous data will be presented as means and standard deviations or medians and interquartile ranges, and categorical data as numbers and percentages. Changes over time in continuous outcomes assessed repeatedly, including the primary sleep outcome, additional sleep-related measures, and health-related outcomes, will be analyzed using repeated-measures analysis of variance (R-ANOVA) or repeated-measures analysis of covariance (R-ANCOVA), as appropriate. Analyses to assess real-world effectiveness within and across the initial treatment arms will include the primary sleep outcome, treatment adherence, health-related outcomes, and resource utilization, using appropriate statistical methods, such as t-tests, chi-squared tests, or analysis of covariance (ANCOVA). When appropriate, age, sex, ADHD medication, and level of ADHD symptoms, will be included as covariates in R-ANCOVA or ANCOVA models. Analyses of long-term follow-up will take into account patterns of treatment use and changes over time, including continued use, discontinuation, switching between treatments, and combined use of weighted blankets and melatonin. Differences in resource utilization will be analyzed through non-parametric analyses of individual data. To address the risk of Type I errors due to multiple comparisons across several outcome measures, Bonferroni corrections will be applied where appropriate.

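### Within-arm CSHQ change is counted as effectiveness without an untreated comparator, so remission and regression to the mean could meet the hypothesis that both arms improve

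*Protocol article*

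**What the plan says.** The first aim, at the end of the Background section, is effectiveness. It covers changes in sleep-related outcomes, adherence, health-related outcomes and "resource utilization within and across the initial treatment arms during the first 12 months after inclusion". The hypothesis that follows expects the arms to differ in pattern, "but that both groups will improve according to the CSHQ total score". The Quantitative methods section uses the same label: "Analyses to assess real-world effectiveness within and across the initial treatment arms will include the primary sleep outcome".

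Four other statements bear on what within-arm change can mean:

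- Study design, on allocation: "Treatment selection will be based on family preference and clinical decision-making in routine clinical practice rather than randomization". Both arms are active and there is no untreated arm.
- Participants and recruitment, on entry: "If at least one of the items fulfills the scoring criteria and is indicated to be a problem, the child is considered eligible for inclusion". The three screening items come from the CSHQ, whose total score is the primary sleep outcome.
- Background, on natural course: "Sleep problems may be transient, but approximately 10% have persistent problems lasting more than one year".
- Participants and recruitment, on the visit at which the screening form is handed out: "If applicable, ADHD medication is also prescribed".

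The Discussion section names as challenges or limitations retention and questionnaire burden, instruments used outside their validated ages, and the lack of a sensory-profile measure. It does not mention natural remission, regression to the mean or the absence of an untreated comparator.

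**The concern.** A fall in CSHQ within one arm is evidence that a treatment works only if little would have changed without it. Here there are several other reasons to expect change. Some problems remit. Children selected on a current positive screen tend to score lower when measured again. Children age. ADHD medication may start around inclusion, and its direction is open, because the Background section says stimulants can cause or worsen sleep problems. Families may also switch or combine treatments, and the article expects only about half of the blanket starters still to use the blanket at one year.

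The hypothesis that both arms improve has no comparator and no threshold, so two inert treatments could satisfy it. This matters because the Background section reports that weighted blankets were restricted to research for lack of evidence of effectiveness, while the project aims to inform guidelines and support implementation. The aim, the hypothesis and the label are all stated in the article, so this is not a detail left to an analysis plan.

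**Working it through.** **The plan's own figure.** Statistical power section: follow-up means 47 and 43, SD 8, two-sided alpha 0.05, power 80%. The normal approximation gives n = 2 × (1.96 + 0.84)² × (8/4)² ≈ 63 per group. The two-sample t-test gives 63.77, rounded up to 64, as stated. A remission rate common to both arms cancels in this contrast, so 64 is unaffected.

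**Inputs from the article.** Baseline mean 53 and SD 8; planned blanket follow-up mean 47, a gain of 6; planned melatonin mean 43, a gain of 10 (Statistical power). Cut-off 48 (section on the CSHQ). About 10% of problems last over a year (Background).

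**Inputs assumed.** The article does not say of whom the 10% is a share, nor what CSHQ score follows remission. Persistence among enrolled children and the remitters' score are therefore varied.

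**Fall with no treatment effect** = (1 − share persisting) × (53 − mean score of remitters).

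| Share persisting | Remitters reach 48 | Share of the 6 points | Remitters reach 47 | Share of the 6 points |
|---|---|---|---|---|
| 10% | 0.90 × 5 = 4.5 | 75% | 0.90 × 6 = 5.4 | 90% |
| 50% | 0.50 × 5 = 2.5 | 42% | 0.50 × 6 = 3.0 | 50% |
| 75% | 0.25 × 5 = 1.25 | 21% | 0.25 × 6 = 1.5 | 25% |

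Two variants:

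- The 10% might be a share of all children with ADHD, of whom the article says: "Among children with ADHD, up to 73% experience sleep problems". Persistence among those with problems is then 10/73 = 13.7%, and the fall to 48 is 0.863 × 5 = 4.3 points.
- If baseline scores are Normal(53, 8) and remission moves only children above 48 down to 48, the mean excess over 48 is 6.30. The fall is 0.90 × 6.30 = 5.7 points with 10% persisting and 0.50 × 6.30 = 3.1 with 50%.

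**Smallest significant within-arm change** = t × SD of change / √n. SD of change = 8 × √(2(1 − r)), which is 8 at an assumed correlation r = 0.5.

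- n = 150: 1.976 × 8/√150 = 1.29 points.
- n = 64: 1.998 × 8/√64 = 2.00 points.

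**Chance that a no-effect fall is significant within an arm (paired t-test).**

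- Fall of 4.5: at least 96% at n = 64 and above 99.9% at n = 150, for r from 0.3 to 0.7.
- Fall of 2.5, r = 0.5: 69% at n = 64 and 97% at n = 150.
- Fall of 1.25, r = 0.5: below the limit at either size, so less likely than not.

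**The case against.** The article is often modest. It speaks of changes over time in a non-randomised cohort, its only powered comparison is between arms, and it credits controlled evidence on blankets to the earlier randomised trial. Expecting both groups to improve is not in itself a causal claim. All this stands and limits the point to labelling and interpretation. It does not remove the point, because the first aim and the Quantitative methods section both place within-arm change under effectiveness. Adjusting for age and ADHD medication, as planned where appropriate, does not separate treatment from the passage of time within an arm.

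The size of untreated change is also open to challenge. A reader might infer that the article's own figures imply nearly the whole planned blanket gain without treatment. They do not:

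- The 10% has no denominator and no CSHQ score attached.
- The 5.4-point result needs remitters to settle at 47, which is the planned blanket mean itself, so 90% of the gain follows by construction.
- The 5.7-point result rests on an assumed score distribution and remission rule.
- Recruitment includes previously diagnosed children, and such prevalent clinic cases probably over-represent lasting problems.
- Entry rests on three items and not on the cut-off. Under Normal(53, 8) about 27% would already score below 48 at baseline.

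Nor does ADHD medication push only towards improvement.

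**Conclusion.** The point holds as one about what may be concluded. As written, the plan could report effectiveness within both arms when neither treatment works. With remitters reaching 48, the no-effect fall ranges from 4.5 points (10% persisting) through 2.5 (50%) to 1.25 (75%), against 6 planned for the blanket. The first two exceed the within-arm significance limits of about 1.3 points (n = 150) and 2.0 points (n = 64); the third does not. These are illustrations: persistence among enrolled children, the score after remission and the SD of change of 8 are assumptions, and the 10% figure applies best to the 12-month visit. It would go too far to say that the hypothesis is certain to be confirmed or that the blanket gain is mostly spontaneous. The powered between-arm comparison and its 64 per group stand.

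**What to change.** 1. In the aims (Background) and in Quantitative methods, describe within-arm change as descriptive change over time and say that it will not be taken as evidence that either treatment works.
2. Restate improvement in both groups as an expectation and not as a test of effectiveness.
3. Rest effectiveness conclusions on the adjusted between-arm contrast, stated as comparative only and open to confounding because families and clinicians choose the treatment.
4. Add natural remission, regression to the mean and the lack of an untreated comparator to the limitations in the Discussion.

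Using the change in the three screening items from screening to baseline as an estimate of untreated change is not recommended. ADHD medication may be prescribed at the visit where the form is handed out, the interval is not stated, and three items cannot stand in for 12-month change in a 33-item total.

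The cost is wording only, with no new data and no change to the sample size. The downside is a more modest claim.

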Follow-up by healthcare professionals at the ADHD unit will be integrated into the standardized care pathway. At inclusion, they will provide information on available treatment options and support families in initiating the selected treatment. During follow-up, healthcare professionals will discuss treatment use, perceived effects, adherence, and possible difficulties. Decisions about treatment continuation, switching, or combined use of weighted blankets and melatonin will be made in dialogue between the family and healthcare professionals as part of routine clinical practice. The standardized care plan for this group is the following: Parents and adolescents aged 15 years or older are offered a one-day course about ADHD. During the first year, follow-up visits are scheduled four weeks after initiation of new medication, and after six months, regardless of medication use. After the first year, the minimum follow-up is a yearly visit up to age 18, with an additional visit if a new medication is introduced. Any anxiety or depressive episodes will be referred to primary psychiatric care up to age 18 years. More complicated psychiatric issues will be referred to the specialized child and adolescent psychiatric services within the same provider. After age 18, the care will be referred to adult psychiatry. If medication is discontinued for more than one year, regular contact with the unit will end, but care can be reinitiated if needed.

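### The predicted arm-specific sleep profile could be produced, or masked, by choice of treatment according to the child's complaint, and the named covariates do not address this

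*Protocol article*

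**What the plan says.** The hypothesis is in the Background: "We hypothesize that the two initial treatment arms will show different patterns of change in sleep-related outcomes during the first 12 months". It is then made specific. For melatonin, "Changes in the standard melatonin treatment arm are expected to primarily concern sleep onset"; for the blanket, "changes in the weighted blanket intervention arm are expected to concern other aspects of sleep, including total sleep time, nightly awakenings, and perceived sleep quality".

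Allocation is described under Study design: "Treatment selection will be based on family preference and clinical decision-making in routine clinical practice rather than randomization". Under Participants and recruitment, a parent-completed screening form asks about slow sleep onset, too little sleep and repeated awakenings. One of the three is enough for entry: "If at least one of the items fulfills the scoring criteria and is indicated to be a problem, the child is considered eligible for inclusion". A nurse assesses the form at the visit where the family is invited. Of the healthcare professionals at inclusion the protocol says that "they will provide information on available treatment options and support families in initiating the selected treatment".

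Quantitative methods compares outcomes within and across the initial arms by repeated-measures ANOVA or ANCOVA, t-tests, chi-squared tests or ANCOVA. It states that, when appropriate, "age, sex, ADHD medication, and level of ADHD symptoms, will be included as covariates in R-ANCOVA or ANCOVA models". No baseline sleep dimension and no screening answer is on that list. The Discussion covers questionnaire burden, validated age ranges and sensory profiles, but not selection of treatment by complaint.

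**The concern.** Two children can both qualify with opposite complaints, one unable to fall asleep and the other waking repeatedly. If the first is more likely to start melatonin and the second a blanket, each arm begins worse on the aspect for which its treatment was chosen. A domain that starts worse has more room to improve and regresses further towards the mean. The melatonin arm would then show the larger fall in onset problems and the blanket arm the larger fall in the others. That is the predicted profile, and it needs no difference in how the treatments work.

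The selection could well run in the predicted direction. The project team expects melatonin to act on onset, the Background reports that its own trial found no actigraphic support for a change in onset with the blanket, and recruitment was planned together with the recruiting clinic. The project is meant to inform personalised care, and a statement about which treatment suits which sleep problem is the finding most directly usable for that.

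**Working it through.** **The plan's own figure.** Follow-up means 47 and 43 with SD 8 give d = 4/8 = 0.50. The normal approximation gives n = 2 × (1.96 + 0.84)² / 0.50² = 62.7, rounded up to 63; the t-test gives 63.8, so 64 per group as stated. This concerns the CSHQ total, not the profile.

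**Model for the profile.** The documents give no dimension-level SDs, correlations or choice rates, so everything in this paragraph is assumed. There are two domains (onset, other), each with baseline SD 1, correlated 0.3. The log-odds of melatonin are g × (onset severity − other severity). Both arms follow the same outcome model, with 150 per arm. The test compares arms on (onset change − other change) at two-sided 5% and counts only significant results in the predicted direction, so the nominal rate is 2.5%.

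**Case (a): regression halfway to the mean.** Follow-up = 0.5 × baseline − constant + error.
- Change then contains −0.5 × baseline. If the arms differ at baseline by δ on onset and by −δ on the other domain, the spurious contrast is 0.5 × 2δ = δ.
- Variance of the contrast per child: 0.25 × (2 − 0.6) + 2 × 0.75 = 1.85. SE = √(1.85 × 2/150) = 0.157.
- At g = 0.5, simulated δ = 0.32, so z = 0.32/0.157 = 2.04 and P(significant) ≈ Φ(2.04 − 1.96) = 53%. Simulation gave 56%.
- Simulated mean changes were −0.58 (melatonin) v −0.42 (blanket) for onset, and −0.42 v −0.58 for the other domain.

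| Selection g | Baseline onset gap δ | (a) Regression to the mean | (b) Equal 30% reduction, no regression | (c) Equal constant shift, no regression |
|---|---|---|---|---|
| 0 | 0 | 2% | not run | not run |
| 0.25 | 0.17 | 19% | 12% | 2% |
| 0.5 | 0.32 | 56% | 32% | 2% |
| 1.0 | 0.55 | 96% | 78% | 2% |

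In case (a) at g = 0.5, a baseline–follow-up correlation of 0.3 gives 68% and one of 0.7 gives 35%. With 64 per arm, case (a) gives 11%, 26% and 64% for the three non-zero values of g.

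**Follow-up values only.** Case (a), g = 0.5: the melatonin arm is worse on onset by 0.5 × 0.32 = 0.16. SE = √(2/150) = 0.115, z = 1.39, and P ≈ Φ(1.39 − 1.96) = 28%; simulation gave 28%. The bias now runs against the hypothesis.

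**A second model with the entry rule.** Entry required a screening score above a threshold on either domain, 60% of the variance was stable, and choice depended on the screening scores. Onset-positive shares of 70 v 56%, 76 v 50% and 85 v 42% (melatonin v blanket) gave false confirmation of 16%, 38% and 80% with no treatment effect. With an equal proportional effect of 40% in both arms the rates were 32%, 79% and over 99%. Independent rebuilds with somewhat different assumptions gave 13–16%, 30–38% and 69–80% without an effect.

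**Which adjustment works.**
- Four covariates unrelated to the complaint: case (a) stays at 19%, 54% and 95%.
- Baseline CSHQ total: unchanged in the second model (17%, 38%, 80% without effect). The reason is simple. Choice depends on onset minus other, and with equal variances this difference is uncorrelated with their sum.
- Baselines of both domains: about 2–3% in the first model; 0–2% in rebuilds of the second, a slight over-correction.
- Baselines of both domains plus the screening answers: 2–3% in the second model.

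**The case against.** The strongest reply is that the premise is not in the documents. They speak only of preference and clinical judgement. The motives they do mention, such as many parents preferring to avoid medication, have no evident link to the complaint. The Background even reports that parents saw faster sleep onset with blankets. This stands: without selection by complaint the artefact is absent.

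A reader might infer that the hypothesis is bound to be confirmed, or cannot be refuted as planned. The figures do not support that. Under weak or medium selection with no treatment effect, the second model fails to confirm in most runs. A constant shift without regression to the mean gives no false pattern, although entry on a positive screen makes some regression likely. A comparison of follow-up values, which the listed t-tests allow, works against the prediction.

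The test used here is also not one that the protocol specifies, and the protocol mentions Bonferroni correction where appropriate. Correcting over the eight CSHQ dimensions reduced one set of no-effect rates from 13%, 30% and 69% to 2%, 10% and 39%. That is a real reduction, but it does not solve the problem under strong selection. Two domains also simplify three overlapping complaints.

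Finally, covariates are often left to an analysis plan, and ANCOVA could include baseline scores. But the article does name a covariate list, and that list leaves out the variables that matter for this hypothesis. The most obvious addition, the baseline total, would not help.

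**Conclusion.** The point holds as a possibility that the stated analysis leaves open, not as a demonstrated bias. If treatment choice follows the complaint, the predicted profile can appear with identical treatments when change is compared, or be hidden when only follow-up values are compared. The rate of false confirmation runs from about 2% to over 90%. It depends on the strength of selection and on how change depends on baseline severity, and the documents fix neither. The 2–3% after adjustment rests on models in which choice depends only on measured severity. A reader might also infer that the main result is compromised. It is not: the primary sleep outcome is the CSHQ total, and neither its analysis nor the sample size is affected by this point. Recommended, not essential.

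**What to change.** In Quantitative methods, state that the profile hypothesis from the Background is tested on the follow-up value of each relevant sleep dimension (onset, duration, night wakings). Each model should adjust for the child's baseline values of all these dimensions and for the three screening-form answers, in addition to the covariates already listed. State that raw within-arm differences between dimensions describe the initial arms and are not read as treatment-specific effects. In the Discussion, name residual confounding by unmeasured reasons for the choice of treatment as a limitation, since the adjustment cannot remove it.

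The cost is a few extra model terms. The screening form and the baseline dimension scores are already collected, so no new data are needed. The wording should be settled before outcome data are analysed.
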